### Patients

#### Baseline measurements

Following the consultation with their GP, a researcher of the study team will immediately conduct the brief baseline interview (~ 10–15 min) with the study (see Additional files 1 and 2). At the beginning of the interview, all patients will be asked about their age, sex, level of education, employment status, and health-related quality of life (EQ-5D [36]).

Patients will then be asked whether they smoke tobacco (cigarettes, hand-rolled cigarettes, pipe, cigar, or hookah). Answer categories will be: (1) “Yes, I currently smoke on a daily” or (2) “on a non-daily basis”, (3) “No, but I used to smoke in the past”, (4) “No, I have never smoked daily or occasionally”.

Current smokers of tobacco products will be asked further details on their smoking behaviour: how long it has been since they had smoked their last cigarette, the average number of cigarettes (or, e.g., pipes, cigars) they smoke per day, week or month (for occasional smokers), on their motivation to stop smoking (German version of the Motivation to Stop Smoking Scale, MTSS [28]), and their strength of urges to smoke (German version of the Strength of Urges to Smoke Scale, SUTS) [39]. These variables represent important co-variates or confounders for the planned statistical analyses.

Subsequently, data on the primary outcome will be collected. Smoking patients will be asked whether their GP started a conversation on the patient’s smoking behaviour during the preceding consultation at the same day. If the answer is “yes”, these patients will be asked whether or not their GP provided brief advice to quit smoking according to either 5A or ABC during the preceding consultation. This is operationalised by whether the GP asked for the smoking status (A1: both 5A and ABC), urged the smoker to quit (A2: both 5A and ABC), asked for the patients’ motivation to quit smoking (A3: only 5A), provided evidence-based stop-smoking therapy (A4: both 5A and ABC) by recommending or prescribing either: individual or group behavioural support (S1), NRT (S2), varenicline or bupropion (S3); and arranged a follow-up appointment (A5: only 5A). Furthermore, recommendations of a combination of therapies will be asked (e.g., “my GP recommended or prescribed me individual or group behavioural support AND NRT).

Patients reporting the receipt of any brief smoking cessation counselling will be asked about their satisfaction with that conversation; operationalised by ratings on a 6-point Likert scale ranging from 1 = “very satisfied” to 6 = “very dissatisfied”).

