**Methods:**

A pragmatic 2-arm cluster randomised controlled trial with a pre-post data collection will be conducted in 48 GP practices in North Rhine-Westphalia (Germany). GPs will be randomised to receive a 3.5-h-training in delivering either 5A or ABC, including peer coaching and intensive role plays with professional actors. The patient-reported primary outcome (receipt of GP advice to quit: yes/no) and secondary outcomes (recommendation rates of smoking cessation treatments, group comparison (5A versus ABC): receipt of GP advice to quit) will be collected in smoking patients routinely consulting their GP within 4 weeks prior, and 4 weeks following the training. Additional secondary outcomes will be collected at 4, 12 and 26 weeks following the consultation: use of cessation treatments during the last quit attempt (if so) since the GP consultation, and point-prevalence abstinence rates. The primary data analysis will be conducted using a mixed-effects logistic regression model with random effects for the cluster variable.

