#### Patients

Patients 18 years or older visiting participating GPs during a study cycle will be asked for to provide informed consent to participate in the study. Patients suffering from moderate or severe cognitive impairment, or those of too low literacy, will be excluded. Moreover, patients who will not talk to their GP in person will be excluded (e.g., patients who just come to pick up a prescription or to escort a relative).

The study team involved in the data collection consists of four part-time researchers (Bachelor/Masters’ degree in psychology, public health, and health economics). Each researcher can manage data collection in two of the eight GP practices in each study cycle. Prior to data collection, the researchers will inform nurses in participating GP practices about the study schedule, and ask for assistance regarding patients who do not meet the inclusion criteria. Posters and leaflets promoting the study will be provided to the practices.

During a data collection day in the practice, patients will be informed about, and invited to participate in the study by the researcher in the waiting room, prior to their consultation with the GP. Consenting patients will be asked to participate in a brief interview immediately following this consultation. At this time, patients will not be fully informed about the real purpose of the study, because addressing the topic of smoking at this time could trigger patients to initiate a discussion about their smoking during the consultation. Hence, prior to the consultation, patients will be asked to participate in a study on “physician-patient communication on health behaviour”. This strategy has been approved by the ethics committee.

Brief interviews (~ 10–15 min) to collect baseline data (see Additional file 1, translated versions are also provided) will be conducted consecutively with every single patient. All patients will be asked on sociodemographic characteristics (e.g., age, sex, level of education), health-related quality of life, and on smoking status. Never and ex-smokers will receive full information on the purpose of the study and the interview will be interrupted at this moment. Patients who only use electronic cigarettes or heat-not-burn products but who do not smoke tobacco cigarettes will also be excluded at this moment. Furthermore, those patients will not be included in any follow-up data collection.

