### Outcomes

#### Primary outcome

The primary outcome is defined as the number of patients who report the receipt of brief stop-smoking advice during the last consultation with their GP, irrespective of the training method, out of the total number of patients who stated to be current tobacco smokers at the time of the consultation with their GP. These data will be collected prior to and following the training through personal interviews in all consecutive patients immediately following GP consultation.

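### The interview asks about advice only if the GP started the talk on smoking, a condition absent from the primary outcome's definition, and the resulting undercount may not be equal before and after training

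*Protocol article*

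**What the plan says.** The Primary outcome section counts the "number of patients who report the receipt of brief stop-smoking advice during the last consultation with their GP" and gives the denominator in these words: "out of the total number of patients who stated to be current tobacco smokers at the time of the consultation with their GP". The abstract gives the same idea as a yes/no item on receipt of GP advice to quit. Neither sets a condition on who brought up smoking.

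Baseline measurements describes how the answer is obtained. First comes the filter: "Smoking patients will be asked whether their GP started a conversation on the patient’s smoking behaviour during the preceding consultation at the same day". A second step follows for some patients only: "If the answer is “yes”, these patients will be asked whether or not their GP provided brief advice to quit smoking according to either 5A" (the sentence then names the other method as well). The items behind the filter are A1 to A5; the A4 items are the secondary outcomes S1-S3. No path is described for a patient who answers no to the filter but was advised.

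Three other statements bear on the point:

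- Analyses of primary and secondary outcome measures recodes a missing primary answer as no advice, and missing S1-S3 as no treatment recommended.
- Intervention says that both trainings teach GPs to ask about smoking (A1) and to advise stopping (A2).
- The Patients section on recruitment withholds the study topic until after the consultation, because naming it "could trigger patients to initiate a discussion about their smoking during the consultation".

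**The concern.** The definition and the measurement describe different quantities. One is advice received; the other is advice received in a conversation that the GP opened. The filtered-out patients remain in the denominator, so the measured rate can only be equal to or lower than the defined one.

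A constant undercount would matter little. Strengths and limitations uses that kind of argument for the presence of the researcher: the outcome is a relative pre-post difference, so a distortion common to both periods does little harm. Here the distortion need not be common. If a patient raises smoking and the GP advises quitting, the consultation has no route to yes. If the trained GP asks first and gives the same advice, it counts as yes. Training acts directly on the filter.

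The primary contrast compares each practice before and after training, and both arms are trained. Randomisation between 5A and ABC therefore cannot remove a shift of this kind. At stake are the primary effect and S1-S3. S4-S9 come from postal questionnaires to all baseline smokers and do not pass through the filter.

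**Working it through.** **Inputs from Power and sample size and from the analysis section:** 48 practices; 8+8 patients per practice for the primary outcome and 21+21 in total (1008 per period); 18% before training; a relevant increase of 10 points; logit SD 0.40 between practices and 0.05 for the time effect; Wald test at 0.05, taken as two-sided.

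**The plan's own figures reproduce.** OR for 18% to 28% = (0.28/0.72)/(0.18/0.82) = 1.77, as stated. A simulation of the stated mixed model (18% to 23% for 5A and 33% for ABC, 8+8 per practice, 400 runs) gives power 0.83, Monte Carlo SE about 0.02, in line with the stated minimum of 80%.

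**Does the text lead to a no?** Set side by side: the advice items follow only a yes to the filter; the denominator is all current smokers; a missing answer becomes no advice. Under each of these rules a patient advised after raising the topic ends as no. This is an inference from three statements; the article does not say it outright.

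**Size, under an assumption.** The documents give no share of patient-initiated advice. Suppose true receipt is 18% in both periods, d points of it are patient-initiated before training, and none are after. The measured rates are then p0 = 0.18 - d and p1 = 0.18. The practice intercept largely cancels within practice, so

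SE = sqrt{ [ 1/(m·p0(1-p0)) + 1/(m·p1(1-p1)) + 0.05² ] / 48 }, with m patients per practice per period,

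and the rejection probability is Φ(logOR/SE - 1.96) + Φ(-logOR/SE - 1.96).

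Worked case d = 0.03, m = 21: log OR = ln[(0.18/0.82)/(0.15/0.85)] = 0.218; SE = sqrt[(0.3735 + 0.3226 + 0.0025)/48] = 0.121; ratio 1.81; rejection 0.44.

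| d (points) | Measured | Spurious OR | Rejection, 21+21 | Rejection, 8+8 |
|---|---|---|---|---|
| 1 | 17% to 18% | 1.07 | 9% | 7% |
| 2 | 16% to 18% | 1.15 | 22% | 11% |
| 3 | 15% to 18% | 1.24 | 44% | 20% |
| 4 | 14% to 18% | 1.35 | 68% | 33% |

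The nominal rate is 5%. For each d, a complete shift is the upper case. If half of the 4 points moved (14% to 16%), OR = (0.16/0.84)/(0.14/0.86) = 1.17; SE = sqrt[(0.3955 + 0.3543 + 0.0025)/48] = 0.125; rejection 24%.

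**Could the filter alone create the planned effect?** Measuring 18% and then 28% with true receipt constant at 28% needs 10/28 = 36% of all advice to be patient-initiated before training and none after.

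**The case against.** The strongest reply is that the interview form sits in Additional files 1 and 2, which are not shown. Baseline measurements is a summary of it, and the form may contain a second route. This stands: a reader might infer that patient-initiated advice is coded no as a fact, but the article supports that only as a consequence of its rules. If the form differs, the summary still needs correcting.

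Second, the sign is not proven. Patient-started talk could rise after training: GPs receive material to pass on, and smokers interviewed before training are told the study's purpose and may come back. The filter would then undercount the later period. This also stands; inflation is the likelier direction because asking first is what is taught, but the documents do not settle it.

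Third, a reader might take the recruitment section as stating that patients do raise smoking themselves. It says only that naming the topic could prompt it, and the concealment guards against that in both periods. How common patient-initiated talk is remains unknown.

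Fourth, asking more often is part of what the training should achieve. That is fair, but the outcome is defined as receipt of advice, so a change only in who speaks first should not count.

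Finally, a reader might infer from "This is operationalised by whether the GP asked for the smoking status (A1: both 5A and ABC), urged the smoker to quit" and the further items that the scoring is open and could decide 5A versus ABC. The documents do not support going that far. The abstract speaks of advice to quit, Background describes the advise step as urging smokers to quit, Intervention labels advising to stop as A2, and the A4 items are split off as S1-S3. All of this points to A2. One confirming sentence is enough.

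**Conclusion.** The point holds as a mismatch between definition and measurement that may bias the primary contrast and S1-S3, probably towards the training. It rests on the article's text without the interview form, on the inferred no coding, and on more GP-started talk after training.

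The 1 to 4 points are an assumption, and the odds ratios of 1.07 to 1.35 and rejection rates of 9% to 68% are the upper case for those values. They show that a modest share would be enough to matter at the planned size; they do not estimate the bias in this trial. The reading that a positive result could be wholly an artefact is not supported: the full 18% to 28% would need about 36% of pre-training advice to be patient-initiated and to vanish as such afterwards.

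**What to change.** **Cycles not yet started.** Ask every current smoker the advice items, whoever raised smoking, and record who raised it as a separate item. The filtered outcome can then still be derived, so all cycles remain comparable on it. Switch only between cycles, so that each practice uses one version before and after training; a practice whose GP is trained one cycle late should keep the version it began with. Report filtered and unfiltered results as a sensitivity analysis.

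**In all cases.** State in one sentence that the primary outcome is A2 = yes, in both arms and both periods.

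**Where all data were collected behind the filter.** Define and report the outcome as advice in GP-started conversations, and limit the conclusion to that.

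**Cost.** One reordered question, one added item and one sentence of definition, but two versions of the instrument across cycles. The room is small: recruitment was still open in January 2019, but on the schedule in Intervention only February/March and May/June 2019 then remained, so at most 2 × 8 = 16 practices could use the new version against 4 × 8 = 32 with the old. The article appeared in July 2019, so the restricted definition may be the only part still available.

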#### Follow-up measurements

Four (time window = + 1 week), 12, and 26 weeks (time windows = + 2 weeks, respectively) after consultation with their GP, patients who reported to be a tobacco smoker at baseline will receive a follow-up questionnaire (see Additional files 3 and 4) by postal dispatch. This questionnaire collects data on secondary outcome (S4-S9): whether or not patients have made an attempt to quit from baseline (GP consultation) to follow-up, and on their current smoking status (S 7-9= point prevalence abstinence rates). In relation to this, questions will be asked about what triggered that attempt (e.g., advice of GP, smoking-related disease, cigarette package health warnings), whether it was supported by evidence-based (e.g., NRT) or non-evidence-based smoking cessation treatments (e.g., acupuncture, hypnosis), and how long this attempt to stop did last (if so). In order to avoid overlaps with further consultations or multiple quit attempts which might have taken place since the initial consultation, the questions will be clearly formulated with reference to specific dates or periods. To assess changes within the health-related quality of life from consultation to follow-up, a paper-based version of the EQ-5D will be sent along with each follow-up questionnaire.

Patients will receive a small unconditional and non-financial incentive together with each follow-up, which is an evidence-based strategy to increase the response rates [43–45].

### Power and sample size

Based on recent data from a study of the German population [13], we assume that about 18% of smokers are currently receiving brief advice on smoking cessation during a consultation with their GP. Training in either the 5A or ABC method is assumed to have a clinically relevant effect if it increases these rates by at least 10% (corresponding to an odds ratio of 1.77) between pre- and post-training.

Calculation of the required sample size is based on the primary analysis and is intended to ensure that a significant time effect between pre- and post-training can be detected with a probability of 80%, taking into account the clustering of patients in GP practices. The following assumptions were made: (a) 48 GP practices will be recruited (six study cycles with 4 GPs receiving the 5A training and 4 GPs receiving the ABC training each cycle); (b) the delivery rate of brief cessation advice prior to the training is 18%; (c) these rates vary among practices with assumed ranges from 9 to 32% in 95% of the practices (corresponding to a standard deviation (SD) of 0.40 on the logit scale); (d) the chance of receiving stop-smoking advice increases on average from 18 to 23% (5A method) or 33% (ABC method) after a training; and (e) varies among practices after the training (between 12 and 40% (5A method) or between 18 and 52% (ABC method) in 95% of the practices (equivalent to a SD of 0.05 for the time effect on the logit scale).

A simulation study based on these assumptions showed that 16 patients (respectively 8 prior to and 8 following the training) per practice are needed to evaluate the primary outcome with a statistical power of at least 80%. A total of 42 patients per practice (21 before and 21 after training) are needed to yield the same power when analysing the interaction between the time and group variable (secondary outcomes S10), resulting in a total study sample size of 2016 patients (respectively 1008 prior to and 1008 following the training). The R-code of this simulation can be provided on request.

Patient participation rates are estimated from data of an earlier study on smoking cessation interventions in GP practices in Germany [46] and on current prevalence rates of smoking in Germany at the moment of developing the study [3]: The number of patients visiting their GP per day is ~ 19, about 28% (*n* = ~ 5) of them are smokers; about 60% of these smokers (*n* = ~ 3) meet the inclusion criteria and are willing to participate in the short interview following the consultation with their GP (primary outcome and secondary outcomes S1-S3). Per study cycle, data collection will be carried out on 7 working days during the 4-week pre-training period and on full 7 working days during the 4-week post-training period, resulting in data from 21 smoking patients prior and 21 smoking patients following the training in each practice (~ 42 smoking patients per practice).

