## Methods/design main trial

### Objectives

The primary objective is to assess the effectiveness of a 3.5-h-training for GPs in delivering brief advice to quit tobacco consumption, irrespective of the training method (5A or ABC), on patient-reported rates of delivery of such advice by their GPs during routine consultations in a German primary care setting.

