#### Analyses of primary and secondary outcome measures

The primary endpoint is dichotomous: patient reported receipt of brief stop-smoking advice delivered by the GP during the preceding consultation (yes or no). Hence, analyses of the primary outcome will be conducted using logistic regression models. Data are structured hierarchically (in clusters = practices), with the patients located within the practices. Since differences in rates of delivery of smoking cessation advice are expected among the practices, mixed effect models will be used. For the primary analysis, the model contains a fixed effect for time (dichotomous: pre- versus post training) and random effects for the practices and the time effect. This model will be adjusted for potential confounders measured at baseline: age, sex, SES, motivation to stop smoking, and strength of urges to smoke of the patients.

The same model will be applied to the secondary outcomes S1-S3 (recommendation of behavioural treatment, NRT, or medication), S4-S6 (patient-reported quit attempts at 4, 12, and 26 weeks following the consultation with the GP), and S7-S9 (patient-reported abstinence at 4, 12, and 26 weeks following the consultation with the GP).

In order to analyse differences between the 5A and ABC training (secondary outcome S10), the group variable (dichotomous: 5A or ABC training) and its interaction with time will be added to the models as fixed effects. In both models, the time effect and the interaction will be analysed by means of Wald tests (level of significance .05).

All participating patients will be included in an intention-to-treat analysis. The risk for missing data on the primary outcome and secondary outcomes S1-S3 will be relatively small, as these data will be collected though personal interviews. However, missing data will be imputed and recoded as patient-reported “no advice-to quit delivered by GP” (primary outcome) and “no treatment recommended or delivered by GP” (S1-S3). To examine the sensitivity of the results, a complete case analysis will be performed additionally, which means that all cases with missing data on the primary outcome will be excluded from the analysis. Missing data on secondary outcomes S4-S6 will be imputed and recoded as “no quit attempt”. Missing data on secondary outcomes S7-S9 will be imputed and recoded as “smoker” at follow-up.

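### The 10-point relevance threshold is worded for either method but fits only the average of 5A and ABC, and the primary model leaves out the randomised method

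*Protocol article*

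**What the plan says.** All references are to the protocol article.

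- **Objectives.** The primary objective is the effect of the training on patient-reported advice, "irrespective of the training method (5A or ABC").
- **Power and sample size, threshold.** "Training in either the 5A or ABC method is assumed to have a clinically relevant effect if it increases these rates". The minimum rise is put at 10%, for which the plan gives an odds ratio of 1.77. That odds ratio fits an absolute rise from 18% to 28%, so the 10% means percentage points.
- **Power and sample size, planning effects.** The starting point is that "the delivery rate of brief cessation advice prior to the training is 18"%. The chance of advice then "increases on average from 18 to 23% (5A method) or 33% (ABC method) after a training".
- **Power and sample size, numbers.** There are 48 practices, 24 per method. The primary test needs 8 patients before and 8 after training per practice. The interaction (S10) needs 21 and 21, and this sets the total of 2016.
- **Analyses of primary and secondary outcome measures.** The primary mixed logistic model has a fixed effect for time, random effects for practice and for the time effect, and patient covariates. Group and its interaction with time enter only for S10. "In both models, the time effect and the interaction will be analysed by means of Wald tests" at the .05 level.

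**The concern.** The threshold sentence names each method, yet one of the two is planned at half the threshold a few lines later. Read literally, the plan expects 5A to miss its own mark of clinical relevance.

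The primary analysis cannot show this. It estimates one pre-post change across all practices and tests it against zero. Because the method is not in the model, the planned difference between arms is absorbed by the random time effect.

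A significant pooled result with a non-significant S10 could then be taken to mean that both trainings reach the relevance mark. The Discussion ties the results to guideline implementation and to a possible method-specific recommendation, so the wording of that conclusion matters.

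**Working it through.** **Inputs from the plan:** baseline 18%; post-training 23% (5A) and 33% (ABC); SD of the time effect 0.05 on the logit scale; 24 practices per arm; 21 + 21 patients per practice; level .05. **Assumptions:** two-sided test (the plan does not say), equal numbers per practice, no covariates.

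**1. The plan's own figures.** (0.28/0.72)/(0.18/0.82) = 1.77, as stated. A mixed-model simulation with a random intercept and random time effect gave pooled power of 78.5% at 7 + 7 and 83% at 8 + 8. The stated 8 + 8 is therefore reproduced and is not in dispute.

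**2. Planned effects against the threshold.**

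| | Rates | Points | Log OR | OR |
|---|---|---|---|---|
| Threshold | 18% to 28% | +10 | 0.572 | 1.77 |
| 5A | 18% to 23% | +5 | 0.308 | 1.36 |
| ABC | 18% to 33% | +15 | 0.808 | 2.24 |
| Average of the two | 18% to 28% | +10 | 0.558 | 1.75 |

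The mean of 23% and 33% is 28%. Only the average meets the mark.

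**3. Standard error of each method's own pre-post change.** The variance of one practice's change is 1/(21 × 0.18 × 0.82) + 1/(21 × p × (1 − p)) + 0.05².
- 5A: 0.3226 + 0.2689 + 0.0025 = 0.594; SE = √(0.594/24) = 0.157.
- ABC: 0.3226 + 0.2154 + 0.0025 = 0.540; SE = √(0.540/24) = 0.150.
- Power for 5A alone against zero: 0.308/0.157 = 1.96, so 50%. The mixed-model simulation also gives 50%.

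**4. What leaving the method out does.** The arms' log ORs lie (0.808 − 0.308)/2 = 0.250 either side of their mean. With no method term, this behaves like extra slope variation with SD 0.25, against the planned 0.05.
- SE of the time effect without arm terms: √(((0.594 + 0.540)/2 + 0.250²)/48) = 0.1145.
- SE of the average effect with time-by-arm, centred coding: ½ × √(0.157² + 0.150²) = 0.1087.
- Ratio 0.949, so the SE is about 5% smaller. If 5A is inert the gain is about 11%.

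Pooled power without arm terms: 0.558/0.1145 = 4.87, so 99.8%.

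**5. Pooled test significant, interaction not.**
- Planned effects: interaction log OR 0.500, SE √(0.157² + 0.150²) = 0.217, power about 63% (62% to 64% in mixed-model runs). The pattern occurs in 36% of trials (20,000 simulated trials with Mantel-Haenszel estimates); a mixed-model simulation with a random intercept only gave 34%.
- 5A inert (18% to 18%), ABC at 33%: the pooled test is still significant in about 88% to 90%. The interaction is then 0.808 with SE 0.223, power about 95%, and the pattern occurs in about 5% of trials.

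**The case against.** **The word 'either' can mean training by whichever method.** That fits the primary objective, and the two planning effects average exactly 10 points. This stands, and it is why the threshold should be stated for the average. The sentence as written does not say so.

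**A pooled primary effect is a declared choice, and S10 covers differences between methods.** This also stands. The pooled test is valid for an average effect, and the sample was raised from 16 to 42 patients per practice for S10. But S10 compares the methods with each other and sets neither against the 10-point mark.

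**The 36% depends on S10 power of about 63%, while the plan states 80%.** If S10 had 80% power, the pattern could occur in at most about 20% of trials. The 63% follows from the plan's rates with the group main effect that the analysis section specifies.

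**Coding and per-method contrasts are analysis-plan detail.** Their absence here is not an error. They belong to the remedy.

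Two stronger readings are tempting, and the documents support neither.
- A reader might infer that a claim of effectiveness under both methods would be false for 5A. Under the plan's own assumptions 5A does raise advice, by 5 points. It falls short only of the 10-point mark.
- A reader might take the 90% pooled significance with an inert 5A as the rate of misleading results. In that case S10 would show the difference in about 95% of trials.

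**Conclusion.** The concern holds in a limited form. The relevance threshold, worded for either method, is consistent with the planning effects only as a threshold for the average over both. The primary model omits the randomised method. This puts the assumed arm difference into the random time effect and lets ABC carry most of a positive result.

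Under the planned effects, about 36% of trials would show a significant pooled effect beside a non-significant interaction. That result would not show that 5A reaches 10 points. The figure rests on 24 practices per arm, 21 + 21 patients, two-sided tests, no covariates and the planned slope SD of 0.05.

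The primary test and its 8 + 8 sample size remain sound for an average effect. What needs correcting is the scope of the threshold, the model terms and the wording of the conclusion.

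**What to change.** 1. State that the 10-point (odds ratio 1.77) threshold refers to the average over 5A and ABC.
2. Include arm and time-by-arm in the primary model, with arm coded -0.5/+0.5. The time term is then the average training effect in both the primary and the S10 model. With 0/1 coding, the time term of the S10 model would be the change in the reference arm only.
3. Report the pre-post change for 5A and for ABC, each with a 95% CI, beside the pooled result.
4. Word the primary conclusion as an average effect over the two methods, not as evidence that each reaches the threshold.

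A rule that bars a claim unless each method's own interval excludes no effect is not advised: 5A alone has only about 50% power for its planned effect.

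Cost: a few sentences and two contrasts, with no extra patients or data. The SE of the average effect becomes about 5% smaller under the planned effects. The downside is a narrower headline claim.

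### The 80% power stated for the 5A-versus-ABC interaction (S10) at 42 patients per practice does not follow from the plan's own inputs and model, which give about 60–64%

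*Protocol article*

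**What the plan says.** All references are to the Protocol article.

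Power and sample size first targets the pre-to-post time effect, which "can be detected with a probability of 80"%, and finds 8 + 8 patients per practice enough. For the between-method comparison it then says "A total of 42 patients per practice (21 before and 21 after training) are needed to yield the same power when analysing the interaction". This second requirement is the larger one, and it produces the total of 2016.

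The assumptions given are:
- "48 GP practices will be recruited (six study cycles with 4 GPs receiving the 5A training and 4 GPs receiving the ABC training each cycle";
- "the delivery rate of brief cessation advice prior to the training is 18"%;
- "the chance of receiving stop-smoking advice increases on average from 18 to 23% (5A method) or 33% (ABC method) after a training";
- SDs on the logit scale of 0.40 between practices and 0.05 for the time effect.

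The section Analyses of primary and secondary outcome measures fixes the S10 model. Starting from a mixed logistic model with random effects for practice and for time, "the group variable (dichotomous: 5A or ABC training) and its interaction with time will be added to the models as fixed effects". It adds that "the time effect and the interaction will be analysed by means of Wald tests (level of significance .05". Sidedness is not stated.

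**The concern.** The sample-size section prints a power figure with all its inputs, and the analysis section prints the model it should belong to. The two can therefore be checked against each other, and they do not agree.

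At stake is the only comparison between the two randomised arms, since the primary outcome is a pre-post contrast. The Discussion says a more specific guideline recommendation can be proposed if one method proves superior. If the assumed difference (23% against 33%) is real, the plan implies a 20% chance of missing it. On its own inputs the chance is nearly twice that.

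**Working it through.** **Inputs.** 24 practices per arm and 21 patients per practice and period give 24 × 21 = 504 patients per arm and period; 4 × 504 = 2016, so the total reproduces. The SDs also fit the printed ranges:
- 9–32%: (logit 0.32 − logit 0.09)/3.92 = 0.398.
- Post-training ranges: 0.405 (5A) and 0.407 (ABC), against √(0.40² + 0.05²) = 0.403.

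Assumed here: two-sided 5% test, no covariates, uncorrelated random effects, equal practice sizes.

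**Primary claim, as a check on the method.** Simulating the planned primary model at 8 + 8 per practice gives about 84–86% power. The stated value of at least 80% holds.

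**S10 in closed form.**
- Effect: logit 0.33 − logit 0.23 = −0.708 − (−1.208) = 0.500.
- Variance: 2/(504 × 0.18 × 0.82) + 1/(504 × 0.23 × 0.77) + 1/(504 × 0.33 × 0.67) + 2 × 0.05²/24 = 0.02689 + 0.01120 + 0.00897 + 0.00021 = 0.0473.
- SE = 0.217; z = 0.500/0.217 = 2.30.
- Power = Φ(2.30 − 1.96) = Φ(0.34) = 63%.

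The practice SD of 0.40 cancels, because each practice is compared with itself.

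**S10 by simulation of the planned mixed model.** Two runs with random intercept and slope gave 62.1% (1500 replicates) and 62.3% (3000). A separate run of the same model gave 59% (500 replicates, Monte Carlo SE about 2 points), and a random-intercept fit gave 64% (2000).

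**Sample size for 80%.** The closed form gives 79.7% at 31 per period and 81.0% at 32. Simulation gives 79% at 32 and 82% at 33. So 32–33 per period are needed: 48 × 64 = 3072 to 48 × 66 = 3168 patients.

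**Can another reading recover 80% at 21 per period?**

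| Variant | Power |
|---|---|
| One-sided test | 74% closed form, 73% simulated |
| Time-effect SD 0 | 63.5% |
| Time-effect SD 0.5 | 48% closed form, 51% simulated |
| Risk-difference scale (not planned) | 76.9% |
| Post-training comparison only (not an interaction) | 77.7% |
| Time and time-by-group, no group main effect | 83% closed form, 81.4% simulated |

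The last line in closed form, per practice on the logit scale:
- Pre-training variance: 1/(21 × 0.1476) + 0.16 = 0.4826.
- Post-training variances: 0.4314 (5A) and 0.3779 (ABC); pre-post covariance 0.16.
- Forcing a common pre-training level gives variance [0.4314 + 0.3779 − 2 × 0.16²/0.4826]/24 = 0.0293, SE 0.171, z = 2.92 and power Φ(0.96) = 83%.

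Simulated power for this model is 79.2% at 20 per period, so it crosses 80% at about the stated 21. Two further simulations at 21 gave 84% (random intercept) and 80% (intercept and slope).

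**The case against.** **S10 is secondary.** The section says the calculation is based on the primary analysis, and the primary claim reproduces. This stands as a limit on the consequences. It does not remove the error, because the total of 2016 is derived from S10.

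**The simulation code is not shown.** It is offered on request, and covariate adjustment was not modelled here. Both are true. But the rates, SDs, cluster numbers and test are all printed, and adjustment is unlikely to close a gap of about 17 points.

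**The planned test protects the comparison.** A reader might infer that the group main effect wastes information and that the plan should switch to a common-baseline model, which recovers about 80% with the same patients. The document does not support this. Under Recruitment, eligibility, and randomisation, method B assigns GPs to an arm by the training date they can attend when registrations are few. That is not random, so equal expected pre-training rates cannot be taken for granted. With the same true training effect in both arms and assumed pre-training rates of 18% and 21%, the common-baseline test rejected in about 9.5% of simulations; with 18% and 23%, in about 22% (400 runs each, random-intercept fit). The planned interaction stayed at about 4–6%. The gaps are assumptions, but they show the direction. Keeping the group main effect is a defensible safeguard, and this part of the objection stands in full.

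**Conclusion.** The power statement for S10 is wrong as written. For the described model at 21 + 21 patients per practice, power is 63% in closed form and about 59–64% in simulation, not 80%. The chance of missing the assumed difference is about 37% (1 − 0.63). This rests on the plan's own rates and SDs, a two-sided test and equal practice sizes; unequal sizes would lower power further.

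Three stronger readings go beyond the document:
- That the trial as a whole is underpowered: the primary claim holds.
- That the trial's simulation certainly omitted the group main effect: the match at 21 per period suggests this but does not prove it.
- That a null S10 will be reported as no difference: the article ties a guideline proposal only to one method proving superior. Low power makes that finding less likely; it does not make a positive one wrong.

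**What to change.** 1. In Power and sample size, restate the power of the S10 interaction test on the primary outcome as about 60–64% at 42 patients per practice.
2. Check the simulation code against the S10 model in the analysis section, and state which fixed effects were simulated. If the group main effect was left out, say so.
3. Keep the unconstrained time-by-group interaction as the main S10 analysis. A common-baseline model may be added at most as a sensitivity analysis, or be limited to cycles allocated by method A. That subset is smaller, so the 80% should not be claimed for it.

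The cost is wording and one check of existing code, with no extra patients or data. Keeping 80% for the planned test would instead need about 3070–3170 patients. At the article's 3 participating smokers per day, 33 per period means 33/3 = 11 collection days per period in place of 7. With recruitment already under way according to the trial status section, restating the power is the realistic course.
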